### Strategies to improve adherence to interventions {11c}

Participants will receive comprehensive education and counseling sessions, which will help them understand the significance of adhering to the prescribed interventions and address any concerns or misconceptions they may have. Investigators will send regular reminders and notifications to participants to ensure they stay on track with the interventions.

### Relevant concomitant care permitted or prohibited during the trial {11d}

Treatment other than “Further intervention” will be prohibited, while treatment for the fellow eye and management of systemic diseases will be permitted.

### Provisions for post-trial care {30}

All follow-up visits will be conducted in the outpatient clinic. After participants withdraw from the study, they will receive standard clinical care. Compensation for any harm caused by the study will be provided by Tianjin Medical University Eye Hospital according to the regulations.

### Explanation for the choice of comparators {6b}

The changes in CST and BCVA are the primary outcomes in this study. BCVA reflects the visual function of patients under the best-corrected refractive state, and it is widely used to evaluate the efficacy of clinical therapy. It is also a primary goal for patients seeking treatment. CST is an anatomical outcome that can reflect macular edema among patients.

### Outcomes {12}

#### Primary outcome

The primary outcome is the changes in BCVA and CST from baseline to month 12 between the two groups.

#### Secondary outcomes

The secondary outcomes include the changes in BCVA and CST from baseline to months 1, 3, and 6; assessment of SRF, location and size of cystoid change, continuity of the IS-OS layer, and presence and quantity of HRF in OCT at months 1, 3, 6, and 12; assessment of FAZ, superficial capillary density (sVD), and deep capillary density (dVD) in OCTA at months 3, 6, and 12; re-treatment and diabetic retinopathy (DR) development from baseline to month 12; cost-effectiveness analysis at month 12; and vision-related quality of life (VRQL) at months 6 and 12.

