### OCT

Three-dimensional spectral domain OCT (DRI-OCT Triton, Topcon, Inc, Tokyo, Japan) will be used to acquire all OCT scans. Scanning was centered on the macular fovea with a scan length of 6 mm. The resolution was 5 μm, the scan depth was 4 mm, and the scan mode was horizontal linear scanning of 512 × 128. CST refers to the average thickness of the distance between the retinal pigment epithelium (RPE) and the ILM at the highest point of the retina, which is measured at a circular area surrounding the foveal center with a diameter of 1 mm. Additionally, we will assess SRF, cystoid size (< 100 μm, 100–200 μm, > 200 μm) and location (outer nuclear layer (ONL) or inner nuclear layer (INL)), IS-OS continuity (completely continuous, partly disrupted, or completely disrupted), and presence and quantity of HRF (< 10, 11–20, > 20), vitreomacular interface (detached, vitreomacular adhesion, vitreomacular traction, and epiretinal membrane). The technicians will ensure that the images are centered and of sufficient quality. OCT images will be analyzed and compared preoperatively and at months 1, 3, 6, and 12.

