### OCTA

OCTA images will be obtained following a standard protocol with the AngioVue OCTA system (RTVue-XR Avanti, Optovue, Fremont, California, USA). The scanning area, centered on the fovea, was captured in 3 × 3 mm sections with a resolution of 304 × 304 pixels. The in-built RTVue XR Avanti AngioVue software will help reveal FAZ, sVD, and dVD through the automated layer segmentation. Motion artifacts, a weak signal (5/10), poorly focused scans, or segmentation failure will all result in poor image quality, which will be disregarded. OCTA images will be analyzed and compared preoperatively and at months 3, 6, and 12.

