### Statistical methods

#### Statistical methods for primary and secondary outcomes {20a}

Descriptive statistics will be used to summarize study results and demographic variables. Means and standard deviations will be used to describe the normally distributed data, and medians and interquartile ranges will be used for non-normally distributed data. Categorical variables will be described as percentage and frequency. The two-sample *t*-test or Kruskal–Wallis test will be used to assess continuous variables, while the chi-square test will be used to evaluate categorical variables. A two-sided *p* value of less than 0.05 will be considered statistical significance. Besides, the records of patients with missing data will be deleted to ensure the accuracy of the results. All the data will be analyzed by SPSS 25.0 (Chicago, IL, USA).

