### Methods for additional analyses (e.g., subgroup analyses) {20b}

Regression analysis will be used for adjusted analysis to control for confounding factors.

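### The tests stated for the OCT and OCTA secondary outcomes cannot take the baseline scan as a covariate; the comparison is valid, but baseline adjustment would sharpen it at no cost in data

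*Protocol article*

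**What the plan says.** **Outcome definitions (Outcomes {12}, Secondary outcomes).** For visual acuity and central thickness the protocol names the quantity: "the changes in BCVA and CST from baseline to months 1, 3, and 6". The same sentence then turns to the imaging markers and gives only visits. For OCT it lists subretinal fluid and cystoid change, followed by "continuity of the IS-OS layer, and presence and quantity of HRF in OCT at months 1, 3, 6, and 12". For OCTA it lists "assessment of FAZ, superficial capillary density (sVD), and deep capillary density (dVD) in OCTA at months 3, 6, and 12". No metric (value, change or adjusted value) is attached to them.

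**Imaging sections.** Under OCT: "OCT images will be analyzed and compared preoperatively and at months 1, 3, 6, and 12". Under OCTA: "OCTA images will be analyzed and compared preoperatively and at months 3, 6, and 12". Neither sentence mentions the arms.

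**Tests ({20a}, headed for primary and secondary outcomes).** "The two-sample *t*-test or Kruskal–Wallis test will be used to assess continuous variables, while the chi-square test will be used to evaluate categorical variables".

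**Additional analyses ({20b}).** "Regression analysis will be used for adjusted analysis to control for confounding factors". No outcome and no covariate is named.

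**Data available.** Table 1 schedules OCT and OCTA at enrolment, so every eye should have a baseline value or grade for each marker.

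**The concern.** The imaging biomarkers are a stated secondary objective. Markers such as FAZ area and vessel density may differ widely between eyes, and an eye's follow-up value may depend on where it started. If so, part of the spread at months 3 to 12 was already visible on the preoperative scan, and an analysis that conditions on that scan can remove it. With about 46 evaluable eyes per arm, the precision is worth having.

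The tests in {20a} leave one route for the baseline scan: building it into the tested variable as a change score. The protocol does this for BCVA and CST but does not say so for the imaging markers. The graded OCT items are the clearest case. A chi-square test of grade by arm uses neither the eye's baseline grade nor the ordering of the grades, and no change category is defined for these items, whereas the BCVA section does define improving, invariant and worsening.

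**Working it through.** **1. Sample size available.** The Sample size section gives 46 per arm before dropout and 51 per arm after it. A non-inferiority calculation with margin 5 letters, SD 9.5, true difference 0, one-sided α 0.05 and power 0.80 (non-central t) gives 46 per arm, with power 0.805, so the stated figure reproduces. It concerns BCVA only. It is used here to supply n = 46; the protocol gives no sample size for the imaging markers.

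**2. Chance baseline difference.** For a continuous marker the standard deviation of the between-arm baseline difference is √(2/46) = 0.21 SD. Under randomisation this is random variation that the standard error of an unadjusted test already covers. It is not a bias.

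**3. Relative variance of the estimated arm effect.** Let r be the correlation between baseline and follow-up, taken as equal in both arms, and set the variance for the raw follow-up value to 1. Then:
- baseline-adjusted (ANCOVA): 1 − r²
- change score, equal SDs at both visits: 2(1 − r)
- saving of ANCOVA against raw value: r²
- saving of ANCOVA against change score: 1 − (1 − r²)/[2(1 − r)] = (1 − r)/2

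The protocol gives no r for any marker, so a range is shown. The last column is the power of the adjusted analysis for an assumed true difference of 0.5 SD (n = 46 per arm, two-sided 5%, non-central t, effect scaled by 1/√(1 − r²)). The raw-value test has power 66% throughout.

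| r (assumed) | ANCOVA variance | Change-score variance | Saving vs raw | Saving vs change | Power, adjusted |
|---|---|---|---|---|---|
| 0.2 | 0.96 | 1.60 | 4% | 40% | 68% |
| 0.3 | 0.91 | 1.40 | 9% | 35% | 70% |
| 0.5 | 0.75 | 1.00 | 25% | 25% | 78% |
| 0.7 | 0.51 | 0.60 | 49% | 15% | 91% |
| 0.8 | 0.36 | 0.40 | 64% | 10% | 98% |

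**4. Reading the table.** Whichever quantity the authors mean to test, adjustment is at least as precise in large samples. A change score is less precise than the raw value when r is below 0.5, so redefining the markers as changes would not be a safe substitute.

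**5. Scope.** The figures apply to FAZ, sVD and dVD. Subretinal fluid, cyst size and location, IS-OS continuity and HRF class are categorical. The argument for using the baseline grade carries over in kind, but these percentages do not.

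**The case against.** The strongest reply is that the protocol never states the analysis a reader might infer, namely that raw follow-up values are compared and the baseline scan is ignored. That reply stands. The outcome wording lists visits and fixes no metric. The test sentence in {20a} also covers BCVA and CST, which are changes, so it cannot show that the other markers are raw values. The OCT and OCTA sections list the preoperative scan among the compared time points and can be read as comparing each eye with itself over time, or as comparing the arms visit by visit.

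Two further points also stand. A reader might infer that a chance baseline gap would bias the treatment comparison; under randomisation it adds variance, and the test's error rate already allows for it. A reader might also infer that much precision is certainly lost. That depends on r, and r could well be low for fluid and cysts, which both treatments aim to clear.

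It can also be said that {20b} already plans adjusted regression, and that covariate lists belong in an analysis plan that is not shown. This carries less weight. The point concerns tests that the article does state, under a heading covering secondary outcomes. The {20b} sentence is an unspecified additional analysis aimed at confounding, whereas baseline adjustment in a randomised trial is done for precision. It does not change which tests serve as the main comparison.

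**Conclusion.** The point holds in a limited form. The tests stated in {20a} cannot take the baseline OCT or OCTA scan as a covariate, the imaging markers are not defined as changes, and the wording leaves open what is compared with what. The resulting comparison would be valid but less precise than it need be. For the continuous markers the variance saving against the raw follow-up value is 4–9% at r = 0.2–0.3, 25% at r = 0.5 and 49–64% at r = 0.7–0.8. These figures rest on assumed correlations that are equal in both arms. The documents do not support a claim that baseline is ignored, that the results would be biased, or that the loss is necessarily large. No sample size or decision rule depends on these markers. This is a free improvement to secondary analyses, not the correction of an invalid one.

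**What to change.** In {20a}:
- Make the between-arm analysis of FAZ, sVD and dVD an ANCOVA at each visit, or one mixed model over months 3, 6 and 12, with that eye's baseline value as covariate.
- Analyse subretinal fluid by logistic regression, and the ordered OCT grades (cyst size, IS-OS continuity, HRF quantity) by ordinal logistic regression. Include the baseline category as covariate where cell counts allow, and state in advance what is done where they do not.
- Report arm effects with 95% confidence intervals.

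In the OCT and OCTA sections, say that the arms are compared at each follow-up visit, adjusted for the preoperative value or grade. If a within-eye comparison over time is also wanted, list it separately.

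The cost is protocol or SAP wording only. The baseline scans are already in Table 1, and the planned software can fit these models.

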### Safety evaluation

Safety evaluation of the study includes any consequences associated with the interventions and course of the disease itself, including ocular hypertension, progression of cataract, corneal abrasion, retinal injury, hyphemia, uveitis or inflammatory reaction, and endophthalmitis.

### Participant timeline {13}

Table 1 outlines the timeline for participant enrollment, interventions, assessments, and visits.

**Table 1 Tab1:** Schedule

	**Study period**										
	**Enrollment**	**Allocation**	**Post-allocation**								**Close-out**
**Time point**	***T***_**1**_	**0**	***T***_**0**_	***T***^*****^_**1(1d)**_	***T***^*****^_**2(1w)**_	***T***_**3(1 m)**_	***T***^******^_**4(2 m)**_	***T***_**5(3 m)**_	***T***_**6(6 m)**_	***T***_**7(12 m)**_	***T***_**x**_
Enrollment:											
Eligibility screen	X										
Informed consent	X										
Allocation		X									
Interventions:											
PPV			X								
IVC			X			X	X				
Assessments:											
Demographics data	X										
Medical history	X										
Laboratory examination	X										
Eye examination	X			X	X	X	X	X	X	X	
BCVA	X					X		X	X	X	
IOP	X			X	X	X	X	X	X	X	
OCT	X					X		X	X	X	
OCTA	X							X	X	X	
Direct medical cost										X	
NEI-VFQ-25	X								X	X	
Adverse events			X	X	X	X	X	X	X	X	

*PPV*, pars plana vitrectomy; *IVC*, conbercept intravitreal injection; *BCVA*, best corrected visual acuity; *IOP*, intraocular pressure; *OCT*, optical coherence tomography; *OCTA*, OCT angiography; *d*, day; *w*, week; *m*, month

^*^Only study group

^**^Only control group

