**Methods:**

This is a single-center, prospective, parallel-group, non-inferiority randomized controlled trial involving 102 DME participants. Participants will be randomly assigned to either the study group (PPV combined with ILM peeling) or the control group (conbercept intravitreal injection (IVC)) at a 1:1 ratio, with a scheduled follow-up at 12 months post-operation. Comparative analysis of results between the two groups will be conducted at months 1, 3, 6, and 12 after the intervention. The primary outcomes involve evaluating the changes in central subfield thickness (CST) and best corrected visual acuity (BCVA). The secondary outcomes include assessment of optical coherence tomography (OCT) and OCT angiography (OCTA) biomarkers, re-treatment and adverse events rates, diabetic retinopathy (DR) development, cost-effectiveness analysis, and vision-related quality of life (VRQL).

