## Interventions

### Intervention description {11a}

#### Control group

Patients will undergo three intravitreal injections of 0.5 mg conbercept (Chengdu Kanghong Biotech Co., Chengdu, China) per month with a 30-guage syringe needle 3.5–4 mm posterior to the corneal limbus under topical anesthesia [46].

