### Intraocular pressure

A non-contact computerized tonometer (CT-1, Topcon, Japan) will be used to measure the intraocular pressure (IOP). The average value obtained from three successive measurements will be noted. An intraocular pressure of at least 25 mmHg or a rise of at least 10 mmHg from the baseline is considered to be ocular hypertension.

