### Adverse event reporting and harms {22}

During each follow-up visit, adverse events will be documented and recorded in the EDC system. Severe adverse events will be reported to Tianjin Medical University Eye Hospital Ethics Committee within 24 h of their occurrence.

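### Day-1 and week-1 safety checks are scheduled only after PPV, so early transient adverse events are ascertained unequally between the arms

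*Protocol article*

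**What the plan says.** All of this is in the protocol article.

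- **Participant timeline {13}, Table 1.** The day-1 and week-1 columns carry marks for eye examination, IOP and adverse events, and are footnoted "Only study group". The month-2 column is footnoted "Only control group". The row "Adverse events" also has a mark at T0, not limited to one arm. IOP and eye examination have none at T0.
- **Control group.** "Patients will undergo three intravitreal injections of 0.5 mg conbercept"; Table 1 places the injections at T0, month 1 and month 2.
- **Adverse event reporting and harms {22}.** "During each follow-up visit, adverse events will be documented and recorded in the EDC system". Severe events go to the ethics committee within 24 hours of occurring.
- **Safety evaluation.** The named events are "ocular hypertension, progression of cataract, corneal abrasion, retinal injury, hyphemia, uveitis or inflammatory reaction, and endophthalmitis".
- **Intraocular pressure.** An IOP of 25 mmHg or more, or "a rise of at least 10 mmHg from the baseline is considered to be ocular hypertension".
- **Abstract and Secondary objectives.** The abstract lists "re-treatment and adverse events rates" among the secondary outcomes, and the secondary objectives include adverse events of both groups. Statistical methods {20a} assigns the chi-square test to categorical variables in general.

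**The concern.** An event that is short-lived and found only by examination enters the count only if somebody looks while it is present. Ocular hypertension as defined here is the clearest case, because without a reading there is no event. Corneal abrasion, hyphema and an inflammatory reaction can also resolve within a month.

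PPV eyes are examined twice in the week after their procedure. Control eyes are not scheduled to be examined until about a month after each injection. If the two arms' rates of such events are set side by side, part of the difference reflects when each arm was examined. The likely direction is an apparent excess for PPV and an undercount after injection. This matters because the trial asks whether PPV could be an initial treatment, and the safety comparison is part of that judgement.

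**Working it through.** **Step 1: scheduled checks, from Table 1 with its footnotes applied.**

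| | T0 | 1 d | 1 w | 1 m | 2 m | 3 m | 6 m | 12 m | Total |
|---|---|---|---|---|---|---|---|---|---|
| Adverse events, PPV | X | X | X | X | – | X | X | X | 7 |
| Adverse events, control | X | – | – | X | X | X | X | X | 6 |
| IOP after baseline, PPV | – | X | X | X | – | X | X | X | 6 |
| IOP after baseline, control | – | – | – | X | X | X | X | X | 5 |
| Control loading injection | X | | | X | X | | | | 3 |

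The totals are close (7 versus 6, and 6 versus 5), so the imbalance is in timing. Between T0 and month 1 there are 2 checks for PPV and 0 for control. None of the three intervals that follow a loading injection (T0 to month 1, month 1 to 2, month 2 to 3) contains a scheduled control check. In the other direction, PPV eyes have no scheduled check between months 1 and 3.

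**Step 2: what this could do to a rate.** The documents give no event rates, so these inputs are assumptions:

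- q is the chance that a transient event is present at a look in the first week after the procedure. It is taken as the same in both arms, at 5% or 10%.
- r = 2% is the chance of such a finding at any routine look.
- Looks are independent, and the control visits at months 1 and 2 count as routine looks.

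The observed proportions with at least one finding are:

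- PPV: 1 − (1 − q)² × (1 − r)⁴
  - q = 5%: 1 − 0.9025 × 0.9224 = 16.8%
  - q = 10%: 1 − 0.81 × 0.9224 = 25.3%
- Control: 1 − (1 − r)⁵ = 1 − 0.9039 = 9.6%

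The ratios are 16.8/9.6 = about 1.7 and 25.3/9.6 = about 2.6. With 51 per arm they correspond to about 9 versus 5 eyes (chi-square p = 0.25, Fisher p = 0.39) and 13 versus 5 eyes (chi-square p = 0.038, Fisher p = 0.067).

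**Step 3: chance of a spurious significant result.** Suppose instead that the true rate of an early transient event is equal in the arms, that PPV detects all of them and control detects a fraction d. With 51 per arm and the uncorrected chi-square test at two-sided 0.05:

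| True rate | d = 1 | d = 0.5 | d = 0 |
|---|---|---|---|
| 5% | 0.044 | 0.077 | 0.251 |
| 10% | 0.049 | 0.147 | 0.764 |
| 20% | 0.050 | 0.286 | 0.995 |

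The d = 0 column is an extreme. Some control events will be caught at T0, at the injection-day visits or through patient complaints.

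**Step 4: shared visits only.** In the step 2 model, restricting both arms to months 1, 3, 6 and 12 gives 1 − 0.98⁴ = 7.8% in each, so the artefact disappears.

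**The case against.** The strongest case on the other side has four parts.

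1. **Control eyes are not unobserved near their injections.** A reader might infer from Table 1 that they are never checked within a month of one. That is not right. Adverse events are marked at T0 in both arms, and the month-1 and month-2 control visits fall on injection days. What stands is narrower: nothing is scheduled between an injection day and the visit one month later, IOP has no mark at T0, and Table 1 does not say whether the month-1 and month-2 readings precede the injection.

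2. **Many events are little affected.** A reader might conclude that adverse-event rates as a whole cannot be compared. The documents do not support that. Cataract progression and other lasting harm can be seen at the shared visits, severe events are reported when they occur, and symptomatic events can be raised by the patient. The problem is confined to early, transient, examination-detected events.

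3. **The size is uncertain, and the main inference is untouched.** Comparisons such as 9.8% versus 0% arise only if control detection is set to zero, and a general claim of a two-fold or larger excess fails in the 5% scenario, which gives about 1.7-fold. The non-inferiority conclusion on BCVA is not affected, and the bias runs against the experimental arm. All of this stands.

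4. **Early checks after surgery are a procedure-specific schedule, and the tested visits could be set in an analysis plan.** The schedule itself is not criticised here. It is also true that the Safety evaluation section names no test and that the chi-square comes from the general methods text. But the article fixes an unequal schedule, ties recording to visits and makes the rates an outcome for both groups. Followed as written, it produces the bias, so this is more than a missing detail.

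**Conclusion.** The point holds in limited form. Early, transient, examination-detected events (ocular hypertension, corneal abrasion, hyphema, inflammatory reaction) are ascertained unequally, and a simple between-arm comparison of their rates would tend to overstate the PPV excess. Under the assumptions in the working, equal true risk appears as about a 1.7-fold or 2.6-fold difference. The direction follows from the schedule; the size depends on assumed values of q and r, on independent looks, and on the month-1 and month-2 control readings not capturing immediate post-injection events.

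The primary outcomes are not involved, nor does this undermine the safety comparison as a whole. It is a cheap improvement worth making before the safety data are compared.

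**What to change.** Add to the Safety evaluation section:

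- The between-arm comparison of examination-detected events uses findings at the visits both arms share (months 1, 3, 6 and 12), plus serious events and events first raised by patient symptoms, at any time in either arm.
- Events found only by examination at an arm-specific visit (day 1 and week 1 for PPV, month 2 for control) are reported in full by arm, without a between-arm test and with a note on the unequal schedule. This includes events that were then treated.

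The last clause is needed. Under Further intervention, postoperative ocular hypertension is treated. A rule that admitted every treated event would bring IOP rises found only at PPV-only visits back into the tested rate, while similar unseen rises in control eyes stayed out.

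The cost is a few sentences, with no new visit or procedure and no change in care. The small downside is that early asymptomatic PPV findings move from the tested rate to a descriptive table. That table must be shown alongside the comparison so that early surgical harm is not hidden.
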